## Methods

### Type of Clinical Trial

We present a randomized, double-blind, placebo-controlled, parallel clinical trial protocol for IN-OT versus PB. We will argue in favor of a multi-method, multi-dimensional (individual and interpersonal strategies) approach to emotion-regulation assessment. We will use two types of attachment paradigms: a conflict discussion with the parent (attachment figure), and the visualization of standardized attachment-related emotional pictures (ie, distress, comfort, joy-complicity, and neutral stimuli) to assess behavioral, neuropsychological, and neurophysiological responses. Although some studies [69-72] have underlined the importance of investigating the effects of IN-OT on adult females, given the risk factors (eg, uterine contraction and menstrual cycle disturbance) for female adolescents in non-clinical environments, this experimental research will be conducted exclusively on healthy male adolescents.

### Study Setting

This study will be conducted in Besançon, France at the University Regional Hospital, in the Department of Adolescent and Child Psychiatry.

### Ethical Criteria

The study will be carried out in accordance with the principles of the Helsinki Declaration. This protocol is governed by French legislation concerning interventional biomedical research and was submitted to the local ethics committee (ie, Comité de Protection des Personnes-EST II) and approved in 2013 (number 2013-000029-29). The study was also approved by the French Agency for the Safety of Health Products (ie, Agence Nationale de Sécurité du Médicament et des Produits de Santé, ANSM) in 2013. The trial is registered with the Clinical Trials Register (NCT02301715). An anonymous identification code will be attributed to each participant in the study, and the list identifying participating patients with their personal data will be stored by the investigator and kept strictly confidential.

### Participants

For this study, 60 French-speaking male adolescents, aged 13 to 20 years, each accompanied by one parent, will be recruited from secondary schools in Besançon, France. Compensation will be given to each adolescent (a €20 gift voucher, Ticket Kadéos Universel, Edenred, France) and to the parent accompanying him (a €20 check).

### Participant Recruitment

To assess eligibility, a pediatric psychiatrist will interview candidate participants using the Attachment Scale Interview (ASI) [73] to determine attachment style. Adolescents diagnosed as insecurely attached will be accepted in the study. Signed consent will be required from both parents and adolescents. The following inclusion and exclusion criteria will be used (Textbox 1).

### Information and Consent

Information packs will be given to adolescents on the day of the first meeting. Information packs will contain two detailed study statements: one for parents, and one for the adolescent. The adolescent’s consent form must be signed by both parents and by the adolescent. The participating parent must sign the parental consent form. The investigator will sign informed consent forms, with a copy for each participant, and the original stored by the investigator. Participants will be informed, in the participant’s information leaflet, that the data generated by the study will be accessible only to the investigator, or to the relevant health authorities for official inspection.

### Material

#### Oxytocin or Placebo Treatment

Syntocinon (NOVARTIS, Basel, Switzerland) is a synthetic, sterile, clear aqueous solution containing a cyclic nonapeptide, identical to endogenous OT released by the posterior lobe of the pituitary. The excipients are sodium acetate, glacial acetic acid, chlorbutanol, and ethanol. The PB will contain all the ingredients in the Syntocinon spray (saline solution) except for OT. Syntocinon and PB sprays, with identical ampoules and labels, will be prepared and randomly assigned by the research pharmacy at the University Regional Hospital Pharmacy of Besançon. Based on studies of IN-OT in adults [74], age-dependent dosage will be used, with age as a proxy for size and weight. Thus, younger participants (aged 13 to 15) will receive 16 international units (IU, 4 puffs of 4 IU), and older participants (aged 16 to 20) will receive 24 IU (6 puffs of 4 IU).

Inclusion and exclusion criteria for participants.InclusionResults of Attachment Scale Interview (ASI): clinical diagnosis of insecure attachmentMale adolescentEnrolled in high school or collegeNot hospitalizedNo current or past history of neurological or psychiatric illness, including substance abuse or dependenceAged 13 to 20 yearsAble to speak and understand FrenchAccompanied by a parentNormal or adequately corrected visionAffiliation to French social securityNot participating in any other ongoing trialsInformed signed consent of adolescent and both parentsExclusionResults of ASI: clinical diagnosis of secure attachmentFemaleIntellectual deficitSevere neurological symptomsKnown allergies to OT or to preservatives in the nasal spray (in particular, E216, E218 and chlorobutanol hemihydrates)Outside of age rangeNot speaking French (either adolescent or parent)Vision problemsChronic disease (ie, liver failure, kidney failure, or cardiovascular disease)Antihypertensive therapySmokingHeavy alcohol use or drug useParticipation in another ongoing trial

**Figure 1 figure1:**
[figure not shown]
Examples of stimulus displays of the four picture categories (distress, comfort, joy-complicity, and neutral).

#### Stimuli

The Besançon Affective Picture Set-Adolescents (BAPS-Ado) [75] will be used to elicit attachment-related emotions. The following categories of emotional stimuli will be used: (1) “distress” (n=20), (2) “comfort” (n=20), (3) “joy-complicity” (n=20), and (4) “neutral” pictures (n=20). The first category of pictures is scenes of distress (ie, faces expressing sadness or anguish, or scenes of loss and separation). The second category is comfort-related scenarios (ie, a parent comforting an infant or an adolescent after an episode of distress). The third is pictures of complicity (ie, joyful moments such as parent-child interaction, and partner or peer interaction). The fourth category is neutral scenes (ie, persons walking along a street or in the subway). Levels of color saturation (50%) and lightness (50%) will be adjusted with Adobe Photoshop (Adobe Photoshop Elements 6.0, Los Angeles, USA). The pictures measuring 11.80 cm in height and 11.50 cm in width will be equiluminant and subtended 10.98° (horizontal) x 11.26° (vertical) of visual angle at a viewing distance of approximately 60 cm. All pictures will be displayed on a black background. Pictures will be pseudo-randomized in blocks. Each block will contain 1 slide with a picture of distress, displayed for 10 seconds, with an inter-stimulus-interval of 2 seconds, followed by 1 slide containing 3 pictures (comfort, joy-complicity, and neutral) presented simultaneously and displayed for 20 seconds. Each block of pictures will be separated by an inter-stimulus interval of 10 seconds (Figure 1).

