### Neurophysiological Measurements

EDA will be measured by skin conductance level (SCL) and SCRs. The SCR will be defined as the maximum change in conductance (in µSiemens) in the 0.1 to 6 second window after stimulus onset. The change in neurophysiological response will be calculated by subtracting mean levels of neurophysiological response SCRs (ie, latency and amplitude) during the baseline from mean levels during each slide viewing, a practice commonly used in neurophysiological research [65,67]. HR will be calculated from the R-R intervals in the ECG.

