### Procedure

First, a psychologist will evaluate the participant’s diagnostic eligibility. Attachment style will be determined using the ASI [74]. Participants who are classified as insecurely attached will return 1 week later for the OT trial (see Figure 2). Randomization will be centralized and performed after the inclusion of the eligible participants. Participants will be randomly assigned to receive either OT or PB intranasally, with both investigators and participants blind to condition. The randomization code will be kept secret by the pharmacy responsible for dispensing the corresponding medication. To reduce bias, randomization will be performed in blocks, with stratification for confounding factors (eg, age). Experiments will be conducted in a comfortable laboratory during the mid-afternoon hours, in accordance with previous research suggesting stability in the diurnal cycle of plasma OT [84]. Each adolescent will first be asked to choose a topic of disagreement to discuss during the parent-adolescent interaction. Then, 45 minutes before the interaction, the adolescent will be instructed to sit and self-administer 1 puff every 30 seconds, alternating nostrils. The adolescent will take each dose in front of the investigator, to assure correct administration and tolerability. The dosage and timing of the nasal spray administration were chosen based on published research on IN-OT, behavior, and emotions in humans [85], and results on cerebrospinal fluid levels after intranasal vasopressin administration [86]. Dyadic interaction will consist of a 5-minute free conversation and a 10-minute conflict discussion that will both be videotaped. The entire interaction session will be transcribed verbatim, and then coded offline for verbal interaction behavior with the GPACS by coders blind to the study hypotheses. After the dyadic stressful interaction, the adolescent will then be isolated in the ET room for 15 minutes, in order to adapt to experimental conditions. The adolescent will be seated in front of the screen in a comfortable viewing position. After this adaptation phase, the EDA electrodes will be fastened to the second phalanges of the index and middle fingers of the non-dominant hand and 2 ECG electrodes will be placed in a bipolar configuration on interior sides of the participant’s wrists [87]. The RED will perform a 9-point calibration procedure. Once this calibration has been successfully accomplished, the 3 minute baseline responses will be recorded with the BIOPAC system. The participant will be informed that the test is due to start, and that he will freely observe a series of 80 pictures. The neurophysiological monitoring AcqKnowledge 4.3 software will be synchronized with Experiment Center 3.0 (RED SMI) software by event markers representing the beginning of each picture. The participant’s eye movements and neurophysiological recordings (EDA and HR) will begin when the first red dot (approximately 0.95° of visual angle) appears. The task will last for about 15 minutes.

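### The three-picture slide starts 2 s after the distress picture ends, so its skin conductance score can carry leftover distress activity and cannot stand as separate evidence of an oxytocin effect

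*Protocol article*

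**What the plan says.** The Stimuli section fixes the order inside a block. One distress picture is "displayed for 10 seconds, with an inter-stimulus-interval of 2 seconds, followed by 1 slide containing 3 pictures" (comfort, joy-complicity and neutral), and these three are "presented simultaneously and displayed for 20 seconds". Between blocks the gap is longer: "Each block of pictures will be separated by an inter-stimulus interval of 10 seconds".

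The Neurophysiological Measurements section takes the SCR as the largest change in conductance "in the 0.1 to 6 second window after stimulus onset". It then subtracts the level "during the baseline from mean levels during each slide viewing", so the three-picture slide is scored as well as the distress slide. The Procedure describes one baseline, before the pictures start: "the 3 minute baseline responses will be recorded with the BIOPAC system". The article describes no reference level taken just before each slide.

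The Type of Clinical Trial section lists all four picture categories as stimuli "to assess behavioral, neuropsychological, and neurophysiological responses". The Secondary Outcome section includes electrodermal activity without limiting it to distress pictures. The SCR prediction in Current Study, a smaller response under oxytocin, concerns distress pictures.

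**The concern.** The three-picture slide never appears except 2 s after a distress picture has gone, so averaging over blocks cannot remove an order effect. The 0.1 s start of the window means that a change already under way when the slide appears can be scored as a response to it. Subtracting a baseline taken before the task does not remove activity left over from 2 s earlier.

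Randomisation does not solve this. The plan itself expects oxytocin to lower the distress response. If that happens, whatever carries over also differs between arms, and the three-picture slide could show an arm difference without evoking anything itself. At stake is one distress effect being reported again as an effect on comfort, joy or neutral pictures.

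**Working it through.** **Inputs from the article.** Distress slide 10 s, gap 2 s, three-picture slide 20 s, gap between blocks 10 s (Stimuli); SCR window 0.1 to 6 s (Neurophysiological Measurements); 80 pictures and a task of about 15 minutes (Procedure); 0.05 Hz high-pass filter on the electrodermal signal (Neurophysiological Measurement Apparatus).

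**Timing reproduces the plan's figure.** 80 pictures at 1 + 3 per block make 20 blocks. 20 × (10 + 2 + 20) s plus 19 or 20 gaps × 10 s = 830 or 840 s = 13.8 or 14.0 min, consistent with about 15 minutes.

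**Scoring windows, with distress onset at 0 s.**
- Distress slide: 0.1 to 6 s.
- Three-picture slide: onset 10 + 2 = 12 s, so 12.1 to 18 s. This is 2.1 to 8 s after the distress picture ends.
- Separation of the two windows: 12.1 − 6 = 6.1 s. They do not overlap.
- For comparison, the next distress window opens 10.1 s after the three-picture slide ends.

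Any carry-over must therefore come from an unrecovered tail or from a late response, including one to the distress picture's disappearance.

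**How much could remain at 12.1 s.** The article gives no recovery time. Assume exponential recovery with half-time h: share left = 0.5^((12.1 − peak time)/h).

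| Peak of distress activity | h = 2 s | h = 10 s |
|---|---|---|
| 3 s | 4% | 53% |
| 6 s | 12% | 66% |
| 10 s (sustained to picture end) | 48% | 87% |

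This is the level remaining, not yet what the SCR rule would score.

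**What the SCR rule would score.** Assumed shape: latency L, then exp(−x/d) − exp(−x/0.75), scaled to a peak of 1, with decay constant d = 2 to 8 s. A response to the distress picture's disappearance of 0, 25% or 50% of that size is added at 10 s. The three-picture slide is assumed to evoke nothing. Scored over 12.1 to 18 s with L = 1.5 s, as a fraction of the distress response:

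| Reading of largest change | Result |
|---|---|
| Range in the window, unfiltered | 0.01 to 0.45 (about 0.24 with a 25% disappearance response) |
| Largest rise, unfiltered | 0 for the tail alone; about 0.04 at 25%; 0.08 to 0.11 at 50% |
| Largest rise, tail alone, after a first-order 0.05 Hz filter | 0.05 to 0.10 |

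The filter shortens the tail but makes the signal undershoot, and the recovery from that undershoot is itself scored as a rise.

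**Arm difference.** Suppose oxytocin cuts the distress response, and any disappearance response with it, by an assumed 30%. At the top of the range the false difference on the three-picture slide is 0.30 × 0.45, or about 0.14 of the distress amplitude. Under the rise reading it is at most 0.30 × 0.11 = 0.03.

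**Test of the remedy.** Counting only rises that begin at 13 s or later gives 0.00 unfiltered and at most 0.007 filtered when L = 1.5 s. With L = 3.5 s, a disappearance response starts at 13.5 s and is counted in full: 0.18 to 0.24 at 25% and 0.42 to 0.49 at 50%, unfiltered. The rule reduces carry-over but does not remove it when responses are late.

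**The case against.** A reader might infer that the second-slide window overlaps the distress response and simply counts it twice. The article does not support that: the scored windows are 6.1 s apart. An overlap of (16 − 12.1)/5.9 = 66% appears only if the 6 s window is also applied to the distress picture's disappearance (10.1 to 16 s). The plan never scores that event, and nothing in the article says it evokes a response.

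Other points on that side also stand. A falling tail is not a rise, so under a rise reading of an unfiltered signal the tail alone adds nothing. The larger figures need the range reading and a 50% disappearance response. The prediction about SCR is tied to distress pictures, and nothing says that second-slide SCR will be claimed as separate evidence. The comparison of arms stays valid as a comparison; only its attribution to the slide is in doubt. This is also a condensed article, and a full protocol may specify a local reference level or a way to separate overlapping responses.

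What remains is what the article does fix: distress first every time, a 2 s gap, a scoring start at 0.1 s, scoring of each slide and a baseline before the task. As written, this rule lets distress activity into the second-slide score, and the high-pass filter does not clear it.

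**Conclusion.** The point holds as a limit on attribution. SCR on the three-picture slide can include residual or late distress activity, and an oxytocin effect found there cannot be separated from an effect on distress. The size is not in the documents. At 1.5 s latency it runs from 0 to about 0.45 of the distress response, depending on how the largest change is read, on the 0.05 Hz filter and on any response to the picture's disappearance. All of these response shapes are assumptions.

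The primary GPACS outcome and the SCR hypothesis on distress slides are not affected by the 2 s gap. Heart rate was not examined here, so nothing is concluded about it. This is an inexpensive improvement to one secondary measure, not a threat to the trial's main result.

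**What to change.** In Neurophysiological Measurements, for all slides, count only rises in conductance that begin at least 1 s after that slide's own onset and within 6 s, with amplitude measured from the level where the rise begins. On the three-picture slide, the earliest counted rise then starts 3 s after the distress picture ends.

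Because this does not catch late responses, add a sentence on interpretation: the oxytocin claim on SCR rests on the distress slides, and second-slide SCR is reported as possibly including recovery from distress, not as separate evidence on comfort, joy or neutral pictures.

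The Abstract reports enrollment as complete, so the slide timing can no longer change. The recordings are continuous and carry event markers, so the new rule is a scoring setting. The cost is that a few true very early responses are dropped and one secondary result is narrowed.

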### Eye-Tracking Apparatus

Eye-tracking (ET) data will be recorded using the Remote Eye-Tracking Device (RED), a non-invasive, contact-free, automatic ET and head movement compensation solution developed by SensoMotoric Instruments (SMI, Teltow, Germany). This system will capture data with temporal sampling at 250 Hz, spatial resolution of 0.03° and high accuracy of visual angle, 0.4°. The RED system will provide reliable binocular and pupil gaze data and allow subjects to wear glasses or contact lenses. The RED system, including Experiment Center 3.0 to control stimulus presentation, iView X 2.8 to control ET data acquisition, and BeGaze to record data, will be interfaced with a Dell laptop. Pictures will be presented on a stand-alone 20 inch monitor (1680 by 1050 pixel screen resolution) placed approximately 60 cm in front of the participant.

### Neurophysiological Measurement Apparatus

A BIOPAC 5 channel acquisition system (BIOPAC System Inc. Model MP 36, Goleta, CA) and a Dell Pentium computer will be used to collect neurophysiological data. AcqKnowledge 4.3 software (BIOPAC Systems, INC. Goleta, CA) will be used to obtain continuous recordings of the participant’s neurophysiological responses (EDA and HR). Two electrodes (BIOPAC Systems Inc., Model EL 507), placed on the second phalanges of the index and middle fingers of the non-dominant hand [76] will be used to record EDA. The EDA data will be digitized at 1000 samples per second, with a gain of 1000. Low (35 Hz) and high (.05 Hz) pass filters will be applied.

Electrocardiograms (ECG) will be collected, together with cardiac impedance, using a two-electrode (2560, 3 M RED DOTTM) configuration with the bio-impedance module for ground referencing. The electrodes will be connected to a BIOPAC ECG module with the gain set to 1000. The waveform will be used to estimate HR using the AcqKnowledge “Hemodynamics” function. HR will be calculated from the R-R intervals in an ECG.

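### The 0.05 Hz high-pass filter on EDA removes the skin conductance level the protocol says it measures, and SCR latency and amplitude, as defined, have no value in the baseline that is to be subtracted

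*Protocol article*

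**What the plan says.** Under Neurophysiological Measurement Apparatus, the article describes the EDA electrodes and then says: "The EDA data will be digitized at 1000 samples per second, with a gain of 1000". The next sentence is "Low (35 Hz) and high (.05 Hz) pass filters will be applied". ECG follows in a separate paragraph with its own gain setting. No second, unfiltered EDA channel is described.

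Under Neurophysiological Measurements, "EDA will be measured by skin conductance level (SCL) and SCRs". The SCR is the maximum conductance change "in the 0.1 to 6 second window after stimulus onset". The change score is then obtained by "subtracting mean levels of neurophysiological response SCRs (ie, latency and amplitude) during the baseline from mean levels during each slide viewing".

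Under Procedure, once the eye-tracker is calibrated, "the 3 minute baseline responses will be recorded with the BIOPAC system". After that, "The participant will be informed that the test is due to start", and the pictures follow. No other baseline is described.

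The Secondary Outcome section covers modification of EDA and heart rate without naming individual EDA measures. The hypotheses under Current Study name SCR amplitude and heart rate.

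**The concern.** Two stated rules do not fit the data they are applied to.

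First, EDA has a slow component (the level, SCL) and a fast one (the responses, SCRs). A 0.05 Hz high-pass filter is a usual way to isolate the fast component, and it does so by discarding the slow one. If SCL is read from the filtered trace, it carries no information about differences between participants or between arms, and a null comparison would say nothing about oxytocin.

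Second, latency is the time from a stimulus to a response. A recording made before any picture is shown has no stimulus to count from, so the latency subtraction cannot be carried out. Amplitude has the same difficulty under the stated definition, because its window is also tied to an onset. An analyst would have to invent a rule after the data are in hand, and SCR amplitude is a measure the hypotheses name.

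**Working it through.** The protocol gives no figure of its own on this point, so there is none to reproduce. The check is on signal processing and on the order of the steps.

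**Inputs from the article.** Cut-off fc = 0.05 Hz. Baseline 180 s. Block timing (Stimuli): 10 s distress slide, 2 s gap, 20 s three-picture slide, 10 s gap, so one block lasts 10 + 2 + 20 + 10 = 42 s. Each block shows 4 of the 80 pictures, giving 20 blocks and 20 × 42 = 840 s = 14 minutes, which agrees with the stated task length of about 15 minutes.

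**Assumptions not in the article.** Filter order 1 or 2 (Butterworth); true SCL of 2 to 15 µS; SCRs of 0.5 µS; slow drift of -0.001 µS per second.

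**Step 1: gain at slow frequencies.** With r = f/fc, the gain is r/√(1 + r²) for order 1 and r²/√(1 + r⁴) for order 2.

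| Component | r | Order 1 | Order 2 |
|---|---|---|---|
| Constant level | 0 | 0 | 0 |
| 840 s period (whole task) | 0.024 | 0.024 | 0.001 |
| 180 s period (baseline length) | 0.111 | 0.110 | 0.012 |
| 42 s period (one block) | 0.476 | 0.430 | 0.221 |

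The zero in the first row does not depend on the filter order.

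**Step 2: a sustained shift in level.** For order 1 the time constant is 1/(2π × 0.05) = 3.18 s. After 10 s, exp(-10/3.18) = 0.043 of a 1 µS shift remains, and after 20 s 0.002. For order 2 the output is -0.152 at 10 s (an undershoot) and 0.008 at 20 s. In neither case does it track the level.

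**Step 3: a simulated trace with the protocol's timing.** After the filter's start-up, mean conductance was:

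| True SCL at start (µS) | Raw baseline mean | Filtered mean, order 1 | Filtered mean, order 2 |
|---|---|---|---|
| 2 | 1.88 | -0.003 | 0.000 |
| 5 | 4.88 | -0.003 | 0.000 |
| 10 | 9.88 | -0.003 | 0.000 |
| 15 | 14.88 | -0.003 | 0.000 |

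The filtered means were the same in baseline and task. The order-1 residual is simply the assumed drift times the time constant, -0.001 × 3.18 = -0.003 µS. A more than sevenfold range in true level leaves no trace.

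**Step 4: the baseline subtraction.** Put the definition beside the sequence of events. The definition needs a stimulus onset. The 3-minute baseline is recorded before the start of the test is announced, so it holds zero picture onsets.

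- Latency = response time minus onset time. With no onset it has no value, and slide latency minus baseline latency is undefined.
- Amplitude = maximum change from 0.1 to 6 s after onset. With no onset the window has no position, so amplitude is undefined under this definition. It would become computable only if a further rule were added, such as fixed windows or spontaneous responses. None is stated.

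**The case against.** The strongest reply is that this is a condensed article. It does not say whether the filter acts at acquisition or offline, and an unfiltered recording may exist from which SCL can be taken. That stands as a limit on the consequence: a reader might infer that the SCL comparison is certain to be a false null, and the document does not establish that. It does not remove the conflict, because the text applies the filter to EDA without distinction and names SCL as an EDA measure.

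The filter sentence names no signal. Its position makes EDA the natural reading. If ECG was meant, the sentence is misplaced and still needs correcting, and the baseline point is unaffected.

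Three other stronger readings are tempting and should not be drawn.

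- That the filter biases the SCR comparison. It does reduce SCR peaks, but by an amount that depends on an assumed filter order and response shape. The same filter applies in both arms, and no between-arm bias or loss of power has been shown.
- That the amplitude change score can never be computed. It can, once a window rule for the rest period is written down. Only latency is beyond rescue, and a short pre-slide baseline would not help it, since that has no onset either.
- That the baseline, being recorded after dosing and after the conflict discussion, subtracts away the treatment effect. The hypothesis concerns reactivity to distress pictures, and change from a rest taken just before them is a reasonable way to address it. A general effect on arousal is a different question, which the article does not pose.

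**Conclusion.** The point holds as an internal conflict with two parts. The stated filter cannot yield the stated SCL measure: the constant level is removed completely at any filter order, unless an unfiltered trace is kept, which the article does not say. The stated baseline correction cannot be carried out for SCR latency, nor for SCR amplitude under the definition given.

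The zero gain at constant level needs no assumption. The simulated means rest on the assumed order, levels, drift and response size. That the baseline contains no stimuli is inferred from the order of steps under Procedure, as is its being the baseline meant in the change score.

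The reach is limited to the EDA part of the secondary outcome. SCL and latency are not named in the hypotheses. SCR amplitude is, and it survives the filter but needs a workable reference. Heart rate, eye-tracking, the primary GPACS outcome and the sample size are not affected. It should be corrected, but it does not threaten the trial's main conclusion.

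**What to change.** 1. State that SCL is derived from the unfiltered (DC-coupled) EDA signal and that the 0.05 Hz high-pass filter is used only to extract SCRs. If no unfiltered signal was stored, delete SCL as a measure.
2. Analyse SCR latency as measured from slide onset, with no baseline subtraction.
3. Score SCR amplitude against the level just before each slide, with the length of that interval fixed in advance. The gap before the three-picture slide is only 2 s, so an interval of at most 2 s would let one rule serve both slide types.

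The cost is a few sentences in the plan and reprocessing of stored recordings. No new data are needed. The only possible loss is SCL itself, if the filter was applied at acquisition and no raw trace was kept.
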